### Unblinding

---

The trial code will only be broken for valid medical or safety reasons e.g. in the case of a severe adverse event where it is necessary for the treating health care professional to know which treatment the participant is receiving before providing appropriate treatment. Subject always to clinical need, where possible, members of the research team will remain blinded. For details on unblinding procedure refer to the trial Randomisation, Unblinding and Code break SOP.

In the event a code is required to be unblinded a formal request for unblinding will be electronically submitted by the authorised investigator to Sealed Envelope using the online unblinding facility, available 24 hours daily. Alternatively, a request to the holder of the code break list, or their delegate, will be made and the unblinded information obtained. The pharmacist and the Trial Co-ordinator will be the solely holders of the code list, other than Sealed Envelope.

If a treating physician, who is not the CI/PI/trial investigator, requires the treatment to be unblinded in an emergency situation, they should notify the Investigating team that an emergency unblinding is required for a trial subject. The investigator/research team will provide this information as quickly as possible. On receipt of the treatment allocation details the CI/PI/trial investigator, or treating health care professional, will deal with the participant's medical emergency as appropriate.

The CI/PI will document the breaking of the code and the reasons for doing so on the CRF/data collection tool, in the site file and medical notes. It will also be documented at the end of the study in any final study report and/or statistical report. The CI/Investigating team will notify the JRO (acting on behalf of the Sponsor) in writing as soon as possible following the code break detailing the necessity of the code break.

The CI/PI will also notify the relevant authorities. The written information will be disseminated to the Data and Safety Monitoring Committee (DSMC) for review in accordance with the DSMC Charter.

Unblinding for the submission of SUSAR reports:

The following procedure will be used to unblind for the submission of a SUSAR report to the regulatory agencies:

- A member of the JRO Sponsor's office will contact the pharmacy requesting unblinding information from the randomisation list.
- The pharmacist will provide their email address and name for the request to be formalised in an email.
- The Sponsor will provide in the email the protocol number and trial name, name of the requester, reason for unblinding, participant's PIN, participant's randomization code and timeline to receive the unblinded information.
- The Sponsor will provide the unblinded information on the e-SUSAR website form.

This information will not be forwarded to the trial team and kept in the JRO site file.

### Visit 1: Screening Assessment

The investigator will contact the participants to follow a standard diet for the 24 hours prior to the scheduled visit day and to avoid alcohol and strenuous exercise. They will fast from 20:00 on the night before the study visit and drink only water. The following screening procedures will be carried out:

- Physical examination.
- Vital signs (heart rate (HR) and blood pressure (BP)).
- Medical history and co-morbidities.

- 
- Concomitant medications.
  - Urine pregnancy test for women of childbearing potential.
  - Weight and height.
  - Blood tests:
    - ✓ Haematology: full blood count, urea and electrolytes.
    - ✓ Serum biochemistry: renal, liver and thyroid function, glucose, lipids, HbA1c.
    - ✓ Gut hormones and adipokines.
  - Meal test will be assessed using our established protocols [25]. Fasted baseline bloods and subjective appetite (assessed using validated visual analogue scores) will be undertaken. At time 0 (t0) a 500 kcal liquid meal will be consumed within 10 minutes. Repeated blood samples and appetite assessments will be made at 15 and 30 minutes. Suboptimal active GLP-1 response is defined as a  $\leq 2$ -fold increase in active GLP-1 circulating levels between time 0 and time 30 minutes.

Once all data related to the screening visit has been obtained, the investigator will review the data to ensure that the participants is eligible to take part in the BARI-OPTIMISE trial. Subjects who are screen-failure will not be re-screened and enrolled in the trial. All screening procedures will be carried out as specified in the schedule of assessments (Appendix 1). An investigator will call the patient to notify of the outcome of screening, answer their questions and explain possible next steps (depending on outcome).

## Visit 2: Baseline Assessment (Day 1)

All participants who have consented for the trial must meet all the inclusion and exclusion criteria as set out in section 6.1 and 6.2. No eligibility waivers or deviations will be permitted. Prior to the scheduled assessment, the investigator will contact the participants to follow a standard diet for the 24 hours prior to the visit day and to avoid alcohol and strenuous exercise. They will fast from 20:00 on the night before the study visit and drink only water. The investigator will also remind participants to complete and bring to the visit the food diary that would have been sent to them (electronically and/or via post) in advance and in preparation for the baseline data collection. The following baseline assessments will be carried out:

- Sociodemographic data.
- Physical examination.
- Vital signs (HR and BP).
- Urine pregnancy test for women of childbearing potential.
- Weight.
- BIA.
- Dual-energy x-ray absorptiometry (DXA) scanning.
- Blood tests:
  - ✓ Haematology: full blood count.
  - ✓ Serum biochemistry: renal, liver and thyroid function, glucose, lipids, HbA1c.
  - ✓ Gut hormone and adipokines.
- Physical function assessments:
  - ✓ 6 minute walk-test (6MWT)
  - ✓ sit-to-stand (STS) test
  - ✓ Hand-grip test

- 
- Physical activity levels using the International Physical Activity Questionnaire (IPAQ).
  - HRQoL questionnaires:
    - ✓ Impact of weight on quality of life-lite (IWQOL-Lite)
    - ✓ Beck depression inventory (BDI).
  - Health Economics questionnaires:
    - ✓ Adapted Client Service Receipt Inventory (CSRI) [26]
    - ✓ EuroQol-5D (EQ-5D) [27, 28]
  - Meal test: fasted baseline bloods and subjective appetite (assessed using validated visual analogue scores) will be undertaken. At t0 a 500 kcal liquid meal will be consumed within 10 minutes. Repeated blood sampling and appetite assessments will be undertaken (T15, T30, T60, T90, T120, T150 and T180). Glucose, gut hormones and adipokines will be monitored using our established protocols [25].
  - Counselling on lifestyle modification (500-kcal deficient diet and 150 minute of physical activity/week).
  - Collection of food diary (3 days of food intake: 2 weekdays, 1 weekend day) completed at home by participants.
  - Distribution of:
    - ✓ New food diary (3 days of food intake: 2 weekdays, 1 weekend day)
    - ✓ Drug diary
  - Subcutaneous injection training. Participants will be contacted by the investigator to assess their injection technique. They will be offered additional injection training by the research investigator as required.

### Treatment procedures

24-week trial of once daily subcutaneously injected escalating liraglutide 3.0 mg or placebo as an adjunct to diet and exercise. Participants will receive on-going counselling for diet and exercise throughout the trial period by healthcare professionals. Liraglutide is a licensed drug. Novo Nordisk will supply liraglutide 3.0 mg and placebo as a solution for injection in a 3 ml pre-filled dial-a-dose pen-injector containing placebo or liraglutide 3.0 mg (6 mg/ml). Study medication will only be administered once all visit 2 assessments have been completed and the relevant safety reports have been obtained. All eligibility criteria have to be fulfilled and no exclusion criteria must be identified.

### Subsequent assessments

#### Visits 3-6: Intervention Phase (Days 15, 29, 57 & 113) (+/- 3 days)

The following will be assessed at each of the trial visits:

Targeted physical examination.

- Vital signs (HR and BP).
- Weight.
- BIA.
- Concomitant medications.
- Drug diary review.
- Adverse event (AE) review.
- Review of glucose monitoring at home.
- Urine pregnancy test for women of childbearing potential.
- Collection of food diary and distribution of new one.

- 
- 389 • Counselling on lifestyle modification.
  - 390 • Review of:
  - 391     ✓ Drug diary
  - 392 • Injection training will be repeated at Visit 3 (day-15), as needed.

#### 393 Visit 7: End-of-Treatment Assessment (Day 169 following the last dose) (+/- 3 394 days)

395 Prior to the scheduled assessment, the investigator will contact the participants to follow a standard  
396 diet for the 24 hours prior to the visit day and to avoid alcohol and strenuous exercise. They will fast  
397 from 20:00 on the night before the study visit and drink only water. The following assessments will  
398 be carried out:

- 399 • Targeted physical examination.
- 400 • Vital signs (HR and BP).
- 401 • Weight.
- 402 • BIA.

#### 403 DXA scanning.

- 404 • Concomitant medications.
- 405 • AE review.
- 406 • Urine pregnancy test for women of childbearing potential.
- 407 • Blood tests:
- 408     ✓ Haematology: full blood count.
- 409     ✓ Serum biochemistry: renal, liver and thyroid function, glucose, lipids, HbA1c.
- 410     ✓ Gut hormone and adipokines.

#### 411 Physical function assessments:

- 412     ✓ 6 minute walk-test (6MWT)
- 413     ✓ sit-to-stand (STS) test
- 414     ✓ Hand-grip test

#### 415 Physical activity levels using the International Physical Activity Questionnaire (IPAQ).

- 416 • HRQoL questionnaires:
- 417     ✓ Impact of weight on quality of life-lite (IWQOL-Lite)
- 418     ✓ Beck depression inventory (BDI).
- 419 • Health Economics questionnaires:
- 420     ✓ Adapted Client Service Receipt Inventory (CSRI)
- 421     ✓ EuroQol-5D (EQ-5D)
- 422
- 423 • Collection of:
- 424     ✓ Food diary
- 425     ✓ Drug diary
- 426 • Meal test: fasted baseline bloods and subjective appetite (assessed using validated visual  
427 analogue scores) will be undertaken. At t0 a 500 kcal liquid meal will be consumed within  
428 10 minutes. Repeated blood sampling and appetite assessments will be undertaken (T15,  
429 T30, T60, T90, T120, T150 and T180) Glucose, gut hormones and adipokines will be  
430 monitored using our established protocols [25].

#### 431 End of Trial Assessment (Day 197) (+/- 3 days)

The investigator will call the participant 4 weeks after the last treatment injection to review and collect any adverse event that might have occurred since end of treatment. This final assessment will be carried out over the phone.

Participants who withdraw before the end of the trial will be asked to attend for their end-of-trial visit (as soon as possible after withdrawal) and their data will be imputed using last observation carry forward (LOCF) method. Withdrawn participants will not be replaced and no follow-up assessment will be carried out.

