### Sample size calculation

Using the 20-week data from the SCALE trial [23], 66 patients (33 per group) will be needed to detect a difference of 5%WL using a two-sample t-test, assuming a common SD of 5.4%, 90% power, 5% statistical significance allowing for a 20% drop-out rate. We anticipate screening between 100 and 150 patients with less than 20% weight loss at one year or more post-surgery. We will consent, recruit and randomise the first 70 patients who fulfil the inclusion and exclusion criteria.

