##### **4.2.1.1 Sample size**

Using the 20-week data from the SCALE trial [1], 66 patients (33 per group) will be needed to detect a difference of 5%WL using a two-sample t-test, assuming a common SD of 5.4% for the intervention (liraglutide + lifestyle) and control groups (placebo + lifestyle), 90% power, 5% statistical significance allowing for a 20% drop-out rate and rounding up. Stata 15 (using sampsi command) was used to perform the sample size calculation [2].

7. 4.2.2 Secondary outcome

The secondary outcomes of this trial are to compare changes in:

1. Fat (%), lean body mass (%) and bone density from baseline visit to end of 24-week treatment period, assessed using DXA scanning and a bioelectrical impedance analyser (BIA), between liraglutide 3.0 mg and placebo.
2. Circulating fasted glucose, insulin, HbA1c and leptin, and meal-stimulated glycaemic, gut hormone and appetite response from baseline visit to end of 24-week treatment period between liraglutide 3.0 mg and placebo.
3. HRQoL (aggregate scores) assessed using CSRI, EQ-5D and IWQOL-Lite from baseline visit to end of 24-week treatment period between liraglutide 3.0 mg and placebo.
4. Characteristics of attitude and symptom of depression (aggregate scores) assessed using BDI from baseline visit to end of 24-week treatment period between liraglutide 3.0 mg and placebo.
5. Physical fitness assessed using 6MWT (distance covered in m), STS test(s) and handgrip test (kg) from baseline visit to end of 24-week treatment period between liraglutide 3.0 mg and placebo.
6. Physical activity level assessed using IPAQ from baseline visit to end of 24-week treatment period between liraglutide 3.0mg and placebo.
7. Healthcare service usage from baseline visit to end of 24-week treatment period between liraglutide 3.0mg and placebo.

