## 10. 5.3 Analysis of the Primary Outcome

The primary outcome is the mean difference in %WL at 24 weeks between the intervention and control groups. The main statistical analyses will estimate the difference in mean %WL between patients randomised to liraglutide + lifestyle and placebo + lifestyle.

Specifically, the following linear regression model will be fitted:

$$\%WL_i = \beta_0 + \beta_1 TRT_i + \beta_2 Baseline\_weight_i + \beta_3 Type_i + \beta_4 T2D_i + \epsilon_i$$

where:

- $\%WL_i$  is the weight loss at 24 weeks for the  $i^{th}$  patient
- $TRT_i$  is an indicator for the allocated treatment for the  $i^{th}$  patient (0 = placebo, 1 = liraglutide)
- $Baseline\_weight_i$  is the weight at baseline for the  $i^{th}$  patient
- $Type_i$  is an indicator for the type of surgical treatment the  $i^{th}$  patient receives (0 = SG, 1 = RYGB) and is one of the stratification factors
- $T2D_i$  is an indicator for diabetes status for the  $i^{th}$  patient (0 = no diabetes, 1 = have diabetes) and is one of the stratification factors
- $\beta_0$  is the regression intercept
- $\beta_1$  is the parameter of interest which quantifies the effect of treatment
- $\beta_2$  is the parameter of interest which quantifies the effect of baseline weight
- $\beta_3$  is the parameter of interest which quantifies the effect of type of surgical treatment
- $\beta_4$  is the parameter of interest which quantifies the effect of diabetes
- $\epsilon_i \sim N(0, \sigma_\epsilon^2)$  are the residuals

The results from this analysis will be presented in terms of a treatment difference ( $\beta_1$ ), 95% confidence interval and a P-value. All analyses will be carried out comparing the intervention and control groups as randomised using all available data (intention to treat analysis). As part of a supportive analysis per protocol and as treated analysis will also be carried out.

Table 1. Primary outcome at 24 weeks

|               | Change at 24 weeks |         | Mean difference between arms (95%) |
|---------------|--------------------|---------|------------------------------------|
|               | Liraglutide 3mg    | Placebo |                                    |
| % Weight loss |                    |         |                                    |

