### 13. 5.5 Missing data/ Drop-out

Where possible, descriptive analysis of the characteristics of patients who withdraw consent will be performed and reasons for withdrawal will be described. A descriptive comparison of drop-out rates between trial arms will be undertaken using tabulations or graphs as appropriate. The characteristics of patients who drop out will be summarised where possible.

Bias due to missing data will be investigated by comparing the baseline characteristics of participants with and without missing values. Depending on the extent of missingness, the predictors of missing values will be identified using logistic regression. As part of a

1124 supportive analysis for the primary outcome, the predictors of missingness related to the  
1125 outcome will be included in the analysis model.

1126 Imputation of missing values of the primary outcome at week 24 may be performed using  
1127 the complete outcome values collected at other measurement time points if considered  
1128 appropriate or using self reported weight. Predictors of missingness and the predictors  
1129 included in the analysis model will be included in the imputation model. The missing values  
1130 will be imputed separately for each randomised group. The handling of missing data for the  
1131 analysis of the secondary outcomes will follow the same strategy if considered appropriate.

1132

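### The protocol's LOCF rule conflicts with the SAP's all-available-data primary analysis, and neither document fixes one method for missing week-24 weights

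*Combined protocol and SAP*

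**What the plan says.** **Protocol, End of Trial Assessment (Day 197).** Participants who withdraw are asked to come in as soon as possible afterwards, and "their data will be imputed using last observation carry forward (LOCF) method". They are not followed further. The rule is unconditional.

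**Protocol, Primary outcome analysis.** %WL at 24 weeks is compared by linear regression on the data available, as randomised. Bias from missing data is to be looked into and handled as appropriate. LOCF is not named.

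**SAP 5.3.** One week-24 %WL value per patient is regressed on treatment, baseline weight, surgery type and diabetes status. The arms are compared "as randomised using all available data (intention to treat analysis". LOCF appears nowhere in the SAP.

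**SAP 5.4.** Patients who withdraw consent leave the primary and secondary analyses from that point, with earlier data normally kept. A random-effects model of %WL over weeks 2 to 24 is planned, but only as a secondary analysis.

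**SAP 5.5.** A supportive model adds predictors of missingness. Then: "Imputation of missing values of the primary outcome at week 24 may be performed using" values from other visits, if thought appropriate, or self-reported weight. Imputation would be done separately by arm. The SAP Introduction places the self-reported-weight analysis among the supportive analyses. SAP 5.5 gives no such label to imputation from clinic visits.

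**SAP 4.2.1.1.** The sample size assumes "90% power, 5% statistical significance allowing for a 20% drop-out rate and rounding up".

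**The concern.** An analyst following the protocol's visit section and one following the SAP would put different values, for different numbers of patients, into the primary model. No section says that LOCF was dropped or which document prevails. The SAP's own imputation is left to later judgement, although SAP 3.1 says the analyses are pre-specified so that the data cannot influence them.

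The methods also fail in different ways. LOCF reports an earlier weight as the 24-week result while weight may still be changing. A regression on completers ignores the interim weights, so it can be biased when leaving depends on the weight change already seen and does so differently in the two arms. The plan gives reasons to expect non-random loss: treatment stops if the full dose is not tolerated (Dose modifications), and persistent non-compliance may lead to withdrawal (Assessment of compliance). The size, and possibly the direction, of any error in the primary estimate is at stake.

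**Working it through.** **1. The plan's own figure.** Inputs from SAP 4.2.1.1: a "difference of 5%WL using a two-sample t-test", "assuming a common SD of 5.4% for the intervention (liraglutide + lifestyle) and control groups", 90% power, 5% significance (taken as two-sided, which is not stated) and 20% drop-out. The standardised effect is 5/5.4 = 0.926. The t-test needs 25.5, so 26 per arm. Then 26/(1 − 0.20) = 32.5, so 33 per arm and 66 in total, which matches "66 patients (33 per group) will be needed". The protocol randomises 70, or 35 per arm. A 20% loss leaves 35 × 0.8 = 28 per arm, with power 92.5% and standard error 5.4 × √(2/28) = 1.44 points. Power is not the problem.

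**2. One patient who withdraws after week 8, under each text.**

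| Source | What enters the primary model |
|---|---|
| Protocol, End of Trial Assessment | Last weight, standing in for week 24 |
| Protocol, Primary outcome analysis; SAP 5.3 | Nothing: no week-24 value, so no row |
| SAP 5.4, if consent is withdrawn | Nothing after withdrawal; earlier weights are kept but unused by the 5.3 model |
| SAP 5.5 | Possibly a value imputed from clinic visits or self-report, possibly nothing |

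If every allowed drop-out lacked a week-24 weight, this would concern 0.20 × 70 = 14 patients.

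**3. LOCF arithmetic.** The documents give no trajectory and no drop-out by arm, so these are assumptions: week-24 losses of 8% (liraglutide) and 3% (placebo), a true on-treatment difference of 5. Let d be the drop-out fraction in an arm and f the share of the week-24 loss reached at the last weight. With drop-out at random within arm:

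estimate = 8 × [(1 − d_L) + d_L × f] − 3 × [(1 − d_P) + d_P × f]

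Example, 20%/20% and f = 0.5: 8 × 0.9 − 3 × 0.9 = 4.50.

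| Drop-out liraglutide/placebo | f = 0 | 0.25 | 0.5 | 0.9 |
|---|---|---|---|---|
| 20%/20% | 4.00 | 4.25 | 4.50 | 4.90 |
| 30%/10% | 2.90 | 3.42 | 3.95 | 4.79 |
| 10%/30% | 5.10 | 5.08 | 5.05 | 5.01 |

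**4. Simulation.** 35 per arm, 4,000 runs, SD 5.4, last weight at week 8 with half the loss reached, unadjusted contrast, true value 5.0. Monte Carlo error is about 0.02. In the response-related rows, leaving becomes likelier as week-8 loss falls, with the drop-out rate in each arm held at the value shown. The last column is single regression imputation by arm from the week-8 weight.

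| Drop-out (liraglutide/placebo) | Completers | LOCF | By-arm imputation |
|---|---|---|---|
| Random, 20/20 | 4.98 | 4.47 | 4.98 |
| Random, 30/10 | 5.02 | 3.97 | 5.03 |
| Poor responders, 20/20 | 4.99 | 4.50 | 5.00 |
| Poor responders in placebo only, 20/20 | 3.99 | 4.25 | 4.97 |
| Poor responders in liraglutide only, 20/20 | 5.96 | 4.72 | 5.00 |
| Poor responders, 30/10 | 5.87 | 4.07 | 4.97 |
| Poor responders, 10/30 | 4.12 | 4.92 | 5.02 |

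Completers and LOCF differ by 0.3 to 1.8 points. The random-loss result for LOCF is similar under another assumed course (effect accruing 12/25/50/85/100% over the five visits): 4.36 to 4.44. Under that course, if one absolute poor-loss rule drives leaving in both arms (placebo 29%, liraglutide 15%), completers give 4.58, LOCF 4.87 and by-arm imputation 5.02.

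**5. A different target effect.** Suppose the target is the effect regardless of stopping, and liraglutide drop-outs return to the placebo mean. At 20%/20% the truth is (0.8 × 8 + 0.2 × 3) − 3 = 4.0. Completers, at about 5.0, are then 1.0 too high, and LOCF (4.0 to 4.9) is 0 to 0.9 too high. A missing-at-random model, also at about 5.0, is no better than completers.

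**The case against.** The firm conflict is one sentence in a visit section against two statistical sections that agree with each other, and the protocol leaves detail to the SAP. A reader might infer three incompatible methods. The documents do not support that count: the protocol's statistics section, SAP 5.3 and SAP 5.5 can be read as one primary analysis with supporting missing-data work. What remains is that LOCF is never withdrawn and that clinic-visit imputation is optional and unlabelled.

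A reader might also infer that both defaults necessarily bias the result. They do not. Completers were unbiased under random loss and under equal response-related loss within each arm, and LOCF was near 5.0 at 10%/30% drop-out.

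The 5.0 benchmark is an on-treatment target, and drop-out was simulated from weights already observed. Both favour the remedy, as step 5 shows. This objection stands, and it is why the target effect must be stated.

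Three lesser points also stand. The 20% is a sample-size allowance, so 14 of 70 is not a forecast. The documents give no drop-out timing, so nothing shows that carried-forward weights would mostly come from dose escalation. Withdrawn participants are asked to attend a visit, but the end-of-trial contact is a telephone call, so it is unclear whether a weight would be taken. Finally, the differences between methods amount to about 0.2 to 1.25 standard errors, all under assumed mechanisms.

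**Conclusion.** The concern holds in a limited form. The protocol's LOCF sentence contradicts the primary analysis in both statistical sections, SAP 5.5 leaves imputation to discretion, and no text reconciles them. The primary estimate is therefore not uniquely specified.

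The choice can move that estimate, but the documents do not show that it will. With 20% overall drop-out and a true on-treatment difference of 5.0, LOCF gives about 4.4 under equal random loss, and in the arithmetic its error runs from −2.1 to +0.1. Completers range from about 4.0 to 6.0 when drop-out depends on response and differs by arm. Using interim weights recovered about 5.0 in every missing-at-random scenario. These figures rest on the assumed losses, trajectory, drop-out pattern and an on-treatment target, none of which the documents give.

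**What to change.** Before unmasking:

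1. Remove the LOCF sentence from the protocol's End of Trial Assessment section, or state in the SAP that it is superseded. Say whether a weight is taken at the early visit and that it is analysed at its actual time.
2. State in SAP 5.3 the target effect of the primary comparison: the effect had participants stayed on treatment, or the effect regardless of stopping.
3. Fix one primary method in SAP 5.3 and 5.5 that suits that target and uses the clinic weights from weeks 2, 4, 8 and 17. Either fit a repeated-measures model with treatment-by-visit terms and report the week-24 contrast, or make by-arm multiple imputation mandatory. Bring the consent-withdrawal text in SAP 5.4 into line.
4. Label the completer regression and any use of self-reported weight as sensitivity analyses.
5. Add one sensitivity analysis in which participants who stop liraglutide lose benefit, because missing-at-random methods estimate the on-treatment course.

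The cost is wording in two documents and slightly more modelling. The weights are already scheduled, SAP 5.4 already plans a random-effects model, SAP 5.5 already sketches by-arm imputation, and the sample size need not change.

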### 503 Dose modifications

504 If participants are unable to tolerate an increased dose during dose escalation, delaying dose  
505 escalation for approximately one additional week will be considered. Liraglutide 3.0 mg/placebo will  
506 be discontinued, however, if a participant cannot tolerate the 3.0 mg dose, as efficacy has not been  
507 established at lower doses. Any dosage changes will be logged in a drug diary by participants and this  
508 will be reviewed at each trial visits.

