### 509 Assessment of compliance

510 Compliance includes both adherences to IMP and Protocol study procedures. Subjects will be  
511 provided with a drug diary to record their home-dosing. Any missed dosage will be logged in the drug  
512 diary. This is a way to assess subject's compliance to the treatment. This will be reviewed at each trial  
513 visit. Percentage of IMP compliance acceptable for patient to continue on the trial is 80%. Non-  
514 compliance will be documented by the investigator in the medical notes and reported to the  
515 sponsor. Persistent non-compliance may lead to subject withdrawal from the study.

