## Outcomes

### Primary Outcome

The primary outcome of this trial is %WL from the baseline visit to the end of treatment visit at 24 weeks. Percentage weight loss will be calculated using the following formula: %WL = [(weight at the baseline visit–weight at the end of the 24-week treatment period )/ weight at the baseline visit] x 100, measured at the end of treatment.

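### Stopping study drug is not separated from leaving the study, so the as-randomised week-24 comparison will lack measured weights for some participants and rests on missing-data rules that differ between protocol and SAP

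*Combined protocol and SAP*

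**What the plan says.** **Outcome and analysis set.** The protocol's Primary Outcome section reads: "The primary outcome of this trial is %WL from the baseline visit to the end of treatment visit at 24 weeks". SAP 5.3 compares the groups "as randomised using all available data (intention to treat analysis"), and the protocol's Primary outcome analysis section likewise takes all available data as randomised.

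**What happens on withdrawal.** The protocol's End of Trial Assessment (Day 197) section says that people who withdraw early "will be asked to attend for their end-of-trial visit (as soon as possible after withdrawal") and that "their data will be imputed using last observation carry forward (LOCF) method". It then adds: "Withdrawn participants will not be replaced and no follow-up assessment will be carried out". The same section describes the end-of-trial assessment as a telephone call about adverse events. Weight is listed at Visit 7, the end-of-treatment visit on Day 169.

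**Routes to withdrawal.** The Assessment of compliance section says "Percentage of IMP compliance acceptable for patient to continue on the trial is 80" per cent, and then "Persistent non-compliance may lead to subject withdrawal from the study". The Dose modifications section discontinues study drug "if a participant cannot tolerate the 3.0 mg dose", without saying whether visits continue.

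**Missing data in the SAP.** Section 5.5 allows, but does not require, imputation of the week-24 outcome from other visits or from self-reported weight, done separately by arm. It does not mention LOCF.

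**The concern.** An as-randomised comparison at 24 weeks is straightforward to interpret when weight at 24 weeks is sought from everyone randomised, whether or not they are still injecting. Here weight collection ends at withdrawal, and withdrawal can follow from poor adherence and perhaps from poor tolerability. Both arise after randomisation, and both can be affected by the allocated treatment. The participants without a week-24 weight may therefore differ between arms in ways related to outcome.

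What is at stake is which question the primary result answers. With few measured off-drug weights at week 24, any method has to supply those values by assumption. LOCF assumes no change in weight after the withdrawal visit. The single week-24 regression in SAP 5.3, fitted to available data, drops these participants. Imputation must borrow largely from people who stayed. A statistician following the protocol and one following the SAP could report different primary estimates.

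**Working it through.** **Inputs.** Difference 5 %WL, SD 5.4, 90% power, 5% significance, 20% drop-out, 66 needed (Sample size calculation; SAP 4.2.1.1). Enrolment 70, 35 per arm (Trial design). Two-sided testing is assumed, as the documents do not state it.

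**1. The plan's own figure.** A two-sample t-test needs 26 per arm (power 90.6%). Allowing for drop-out, 26 / 0.8 = 32.5, rounded up to 33 per arm, or 66. The stated figure is reproduced.

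**2. Participants affected.** 0.20 × 70 = 14, or 7 per arm, leaving 28 per arm with a week-24 weight. This is an upper figure for what the withdrawal rule causes, because the 20% is not broken down by reason.

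**3. Power and precision.** With 28 per arm, power for 5 points is 92.5%. The unadjusted standard error is 5.4 × √(2/28) = 1.44 points. With all 35 per arm weighed it would be 5.4 × √(2/35) = 1.29, which is the best case.

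**4. Illustration of the gap between two estimands.** Let a fraction d in each arm stop drug, let those who stop keep a fraction r of the 5-point effect, and let completers show 5 points. The treatment-policy effect, which counts everyone at week 24 regardless of drug use, is 5 × (1 − d + d × r). The completer estimate exceeds it by 5 × d × (1 − r). The documents give no value for r; 0 to 0.5 is assumed.

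| Drop-out d | Effect, r = 0 | Effect, r = 0.5 | Completer excess |
|---|---|---|---|
| 10% | 4.5 | 4.75 | 0.25 to 0.5 |
| 20% | 4.0 | 4.5 | 0.5 to 1.0 |
| 30% | 3.5 | 4.25 | 0.75 to 1.5 |

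**5. Power if everyone were weighed.** With 35 per arm and 20% stopping drug, power is 86.3% for an effect of 4.0, 90.1% for 4.25 and 93.0% for 4.5. Full follow-up may cost a little power through dilution of the effect. Its gain is that the estimate answers the as-randomised question.

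**6. The two documents side by side.**

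| Point | Protocol | SAP |
|---|---|---|
| Week-24 value after withdrawal | LOCF, stated as a rule | Available data; imputation optional |
| Source of the value | Last observation | Other visits or self-reported weight |
| Stopped drug, consent not withdrawn | Not defined | Counted as a separate category in the CONSORT template; follow-up not defined |

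**The case against.** A reader might infer that the intention-to-treat analysis cannot be done. The documents do not support that. The SAP defines it as an as-randomised comparison of all available data, and that can be computed.

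A reader might also infer that anyone below 80% compliance is removed. The text says only that persistent non-compliance may lead to withdrawal. Nor is it established that people who stop for intolerance go unweighed at week 24: the Dose modifications section is silent on visits, and the SAP's CONSORT template counts discontinued intervention separately from loss to follow-up. For that group the defect is ambiguity.

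The plan also makes some provision for missing data: LOCF in the protocol and, in the SAP, optional imputation by arm, a supportive model with predictors of missingness, and a random-effects model of %WL using the interim visits. SAP 5.4 excludes only those who withdraw consent, and only from that point. Calling the withdrawal visit an end-of-trial visit may be a labelling slip, since participants are asked to attend.

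These objections limit the claim but do not remove it. The absence of follow-up after withdrawal is a stated rule, the link from non-compliance to leaving the study is written down, and none of the analysis methods replaces a measured off-drug weight at week 24.

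**Conclusion.** The concern holds in this form: followed as written, the plan does not seek a week-24 weight from withdrawn participants, who may include people withdrawn for reasons that treatment can affect. At the planned drop-out, the primary comparison rests on missing-data assumptions for up to about 14 of 70 participants, and the protocol and SAP differ on those assumptions.

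The 0.5 to 1.0 point gap is tempting to read as the bias of the planned analysis, but it is not. It contrasts completers with a treatment-policy effect under an assumed retained fraction. LOCF would bring in the early weights, and its bias depends on when people leave and on their later weight, which the documents do not give. Some of the 20% may also be consent withdrawal or loss to follow-up, which no protocol wording would recover; for the same reason the standard error would move from 1.44 towards, and at best reach, 1.29. Power is not the problem. The issues are bias and which effect is estimated.

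**What to change.** - In the End of Trial Assessment section, define stopping study drug and withdrawing consent to follow-up as separate states. Invite everyone who stops drug, for any reason, to Visit 7 on Day 169, with weight as the minimum, unless they withdraw consent to follow-up.
- State that the visit at withdrawal includes a weight, correct its name, and record that weight under its actual date.
- Reconcile the two compliance statements (the 80% level for continuing, and possible withdrawal for persistent non-compliance) so that non-compliance does not end outcome collection. No rule for stopping study drug needs to change.
- Name one primary missing-data method, identical in both documents, and present the alternatives as sensitivity analyses.

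**Cost.** A short protocol amendment, a matching SAP edit, and up to about 14 attendances that are already in the schedule. Some participants will decline.

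SAP Version 4 is dated February 2021, so follow-up may already be complete. In that case, report the primary result as relying on missing-data assumptions rather than as a full intention-to-treat comparison, and give the number in each arm without a measured week-24 weight.
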